## Abstract

**Background:**

Frequently, the women affected by the genitourinary syndrome of menopause experience genitourinary dysfunctions that profoundly influence their overall health. Even though the symptoms do not jeopardize the women’s lives, the urinary and sexual dysfunctions significantly impact their quality of life. Isolated treatments focused on the main causes of the dysfunctions, such as pelvic floor muscle training (PFMT) and photobiomodulation have shown significant improvements in genitourinary dysfunctions. So, the association of PFMT with photobiomodulation may generate additional effects in the genitourinary area. This study aims to create a PFMT protocol isolated and associated with photobiomodulation therapy in women affected by the genitourinary syndrome of menopause.

**Methods:**

It is a randomized, controlled, double-blind clinical trial protocol study that will include women experiencing genitourinary symptoms related to menopause, sexually active, never practiced pelvic floor muscle exercise or photobiomodulation treatment, and do not use hormone replacement therapy for at least 3 months. The randomization will allocate the women to three groups: PFMT group, PFMT associated with active intracavitary photobiomodulation group, and PFMT associated with sham intracavitary photobiomodulation group. A total of 16 sessions will be conducted twice a week. The assessments will occur before interventions, after the sixteenth session, and 1 month after the sixteenth session (follow-up). The evaluation will include the pelvic floor muscle vaginal manometry as the primary outcome. Also, the international consultation on incontinence questionnaire—short form, the female sexual function index, the Utian Quality of Life scale, the patient global impression of improvement, the modified Oxford scale, and the vaginal health index will be the secondary outcomes.

**Discussion:**

Despite there are gold standard treatments such as PFMT, to alleviate genitourinary symptoms, interventions mirroring clinical practice are needed. This study protocol might show a groundbreaking and viable method to potentiate the effects of a gold-standard treatment associated with photobiomodulation.

**Conclusion:**

We expect this protocol to demonstrate that the use of PFMT and photobiomodulation strategies is feasible and able to potentiate the recovery of women affected by the genitourinary syndrome of menopause. The Ethics Committee of the Federal University of Rio Grande do Norte approved the study (n° 6.038.283), and the clinical trials platform registered the protocol (n° RBR-5r7zrs2).

## Introduction

The genitourinary syndrome of menopause (GSM) is characterized by the presence of signs and symptoms generated from estrogen deficiency in the female genitourinary tract, involving the vagina, labia, vestibule, urethra, and bladder (Portman, Gass & Vulvovaginal Atrophy Terminology Consensus Conference Panel, 2014). Approximately 40% to 50% of women in physiological menopause experience symptoms associated with the GSM (Portman, Gass & Vulvovaginal Atrophy Terminology Consensus Conference Panel, 2014; Palacios et al., 2017). The main signs and symptoms include vaginal atrophy and dryness, vulvovaginal discomfort, and sexual difficulties, such as lack of lubrication and dyspareunia (Portman, Gass & Vulvovaginal Atrophy Terminology Consensus Conference Panel, 2014). Furthermore, the GSM is associated with atrophic changes in the vaginal mucosa, reduction of Lactobacillus levels in the vaginal microbiota, and urinary dysfunctions, significantly impacting women’s overall health and quality of life (Chedraui et al., 2012).

Pelvic floor muscle training (PFMT) is a recommended strategy to treat the GSM (Abrams et al., 2010). There is evidence demonstrating that pelvic floor muscle training improves corporal conscience and strengthens the pelvic muscles, decreasing urinary dysfunctions and enhancing desire, excitement, and orgasm, which are important in female sexual activity (Rosenbaum, 2005). Recently, photobiomodulation has emerged as a therapeutic approach to treat common dysfunctions in the genitourinary syndrome of menopause (Frederice et al., 2022; De Marchi et al., 2023). Some experimental studies showed that the photobiomodulation therapeutic effect is related to photo absorption from specific tissues, such as chromophores (Karu & Kolyakov, 2005). Also, photobiomodulation can induce the expression of regulatory proteins from the cell cycle, activating satellite cells, promoting angiogenesis, increasing the quantity and density of the regenerator fibers, and stimulating mitochondrial activity (Ferraresi et al., 2011; Iyomasa et al., 2009).

Considering these assumptions, photobiomodulation has been utilized to prevent muscle damage, repair muscle tissues, improve muscle performance, and reduce fatigue (Xu et al., 2018; Toma et al., 2016; Ferraresi et al., 2015; Lanferdini, Krüger & Baroni, 2018). Moreover, the chronic use of photobiomodulation associated with strength exercise training potentiates the strengths generated by the exercise (Ferraresi, Huang & Hamblin, 2016; Vanin et al., 2016; Baroni et al., 2014; Ferraresi et al., 2011). Evidence demonstrates that the photobiomodulation intervention before or after an 8-week muscular training potentiated the muscular thickness and strength (Ferraresi, Huang & Hamblin, 2016; Vanin et al., 2016; Baroni et al., 2014; Ferraresi et al., 2011; Vassão et al., 2018). The therapeutic effects generated by photobiomodulation have been associated with improvements in fatigue reduction, post-exercise recovery, and muscular performance (Baroni et al., 2014; Ferraresi et al., 2011; Miranda et al., 2016).

Although pelvic floor alterations, such as urinary and sexual dysfunctions do not threaten women’s lives, they generate significant limitations (Levine, Williams & Hartmann, 2008). In this sense, urinary and sexual dysfunctions impose physical, social, and occupational restrictions, affecting the women’s quality of life (Levine, Williams & Hartmann, 2008). Therefore, it is important to investigate the effects of innovative therapies to treat the dysfunctions generated by the GSM in order to improve women’s health and quality of life.

Considering the photobiomodulation physiological effects on the pelvic floor muscle and the scarcity of clinical trials related to this subject, this preliminary study aims to explore the feasibility and therapeutic window for PFMT isolated and associated with photobiomodulation in women affected by GSM who present urinary and sexual dysfunctions.

## Methods

### Study setting

It is a randomized, controlled, double-blind clinical trial protocol study that will be performed at the urogynecology outpatient clinic located in the Maternity Hospital Januário Cicco School from the Federal University of Rio Grande do Norte, Natal, Brazil, in 2024.

### Eligibility criteria

We will recruit women to participate in this study according to the following criteria: (1) age between 45 and 65 years old; (2) natural menopause at least 1 year ago; (3) no use of hormone replacement therapy for at least 3 months; (4) sexually active; (5) present sexual dysfunction identified by the female sexual function index with a score higher than 26.55 points; (6) present urinary incontinence (UI) identified by the international consultation on incontinence questionnaire (short form) with a score higher than 1 point; (7) never having performed exercises for the pelvic floor muscles; (8) never having participated of photobiomodulation treatment; (9) presenting a negative Pap smear result for cervical cancer precursor cells in the last year.

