### Outcomes

After the inclusion criteria, the included women will start the first evaluation before interventions. Then, there will be another evaluation after the twelfth and twenty-fourth session (midpoint and final evaluations). Another evaluation will occur 1 month after the end of the interventions (follow-up). The women will answer some questionnaires and perform physical and functional tests related to the pelvic floor muscles in accordance with the published license. Figure 1 illustrates the study flow diagram.

The primary outcome will involve measuring pelvic floor muscle vaginal manometry. The device Peritron, model 9300AV, will evaluate the pelvic floor muscle pressure. Initially, the evaluator will instruct the women to empty their bladder and remain in the lithotomy position. A conical sensor probe introduced in the vaginal canal will capture the pressure generated by the pelvic floor muscle. During the test, the evaluator will instruct the women to perform three maximum pelvic floor muscle contractions without contracting the abdominal, hip adductor, and gluteal muscles. The interval between the contractions will last 30 s. We will calculate the three attempts average and classify them according to the following criteria: very weak (7.5–14.5 cmH_2_O), weak (14.6–26.5 cmH_2_O), moderate (26.6–41.5 cmH_2_O), good (41.6–60.5 cmH_2_O) and strong (>60.6 cmH_2_O) (Angelo et al., 2017).

The international consultation on incontinence questionnaire – short form (ICIQ-SF) will evaluate UI; the female sexual function index (FSFI) will evaluate sexual function; the Utian Quality of Life (UQOL) scale will evaluate quality of life; the patient global impression of improvement (PGI-I) will evaluate the perception of improvement; the modified oxford scale will evaluate pelvic muscle strength; and the vaginal health index (VHI) scale will analyze vaginal atrophy. They will feature as secondary outcomes in the study’s evaluation.

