The ICIQ-SF is a self-administered questionnaire that classifies urinary loss. The questionnaire is translated and validated in the Portuguese language (Tamanini et al., 2004). It presents four questions that evaluate the frequency, severity, and impact of UI on quality of life. It also presents a set of eight self-diagnostic items that allow evaluation of UI causes or situations experienced by patients. Only the first three questions will be scored and the total score will range from 0 to 21 points. The impact on quality of life will be classified as no impact (0 points); light impact (1 to 3 points); moderate (4 to 6 points); severe (7 to 9 points), and very severe (10 or more points) (Tamanini et al., 2004).

The FSFI is a self-administered questionnaire validated in the Portuguese language and Brazilian population. It presents nineteen questions about sexual activity during the last 4 weeks, involving six domains: desire, excitation, lubrication, orgasms, satisfaction, and discomfort/pain. The total score requires the domain’s sum. Scores below 26.55 points will classify as sexual dysfunction (Thiel Rdo et al., 2008).

The UQOL scale evaluates the quality of life, specifically for menopausal women. It is validated and adapted for Brazilian women and presents 23 questions divided into four domains: occupational, health, emotional, and sexual. The score spans from 23 to 115, with a higher score indicating a better quality of life (Utian et al., 2002; Lisboa et al., 2015).

The PGI-I is a simple and easy-to-use scale that presents clinical applicability to the perception of the intervention. It presents a single question about urinary functioning compared to the period before intervention. The score ranges from 1 (very much better) to 7 (very much worse) (Yalcin & Bump, 2003).

The modified Oxford scale evaluates the pelvic floor muscle through a manual palpation to measure the pelvic floor muscle strength. The scale presents six points to quantify the pelvic floor muscle strength according to the following criteria: grade 0: no contraction; grade 1: small and no sustained contraction; grade 2: low intensity and sustained contraction; grade 3: moderated contraction, feeling the intravaginal pressure compressing the evaluator’s finger; grade 4: satisfactory contraction, the evaluator’s fingers are compressed by the intravaginal pressure; grade 5: strong contraction, the evaluator’s fingers are compressed towards to pubic symphysis (Da Roza et al., 2013).

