### Sample size

G-Power software version 3.1.9.2 calculated the sample size, according to the ANOVA F test repeated measures, within-between interaction, based on a previous study (Bezerra et al., 2020). We considered the data from the manometry results between groups after interventions. To calculate, we will consider a power of 80%, an alfa error of 5%, and an effect size of 0.23. Therefore, a total of forty-two individuals will participate in the study.

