## Conclusion

PFMT associated with photobiomodulation protocol is expected to amplify the effects of isolated PFMT in women experiencing GSM accompanied by urinary and sexual dysfunctions. Also, we project that this combined protocol mirroring clinical practice is feasible for women. This preliminary study intends to explore the feasibility and initial trends for PFMT associated with photobiomodulation.

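### The FSFI entry threshold points the wrong way: criterion 5 admits only women whom the protocol itself classifies as free of sexual dysfunction

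*Protocol article*

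**What the plan says.** In the protocol article, Eligibility criteria, item 5 requires that women "present sexual dysfunction identified by the female sexual function index with a score higher than 26.55 points".

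The Outcomes section, where it describes the FSFI, states: "Scores below 26.55 points will classify as sexual dysfunction".

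The target population is described the same way elsewhere. The aim at the end of the Introduction is to study the treatments "in women affected by GSM who present urinary and sexual dysfunctions", and the Conclusion speaks of "women experiencing GSM accompanied by urinary and sexual dysfunctions".

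The FSFI has two roles. It decides entry, and it is a secondary outcome: "the female sexual function index (FSFI) will evaluate sexual function".

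**The concern.** The eligibility list and the Outcomes section give the same label to opposite sides of one cut-off. Screening is done by threshold, so a direction error in the threshold decides who enters. Followed by its number, item 5 turns away the women the trial is about and enrols those who do not have the problem.

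Two things are at stake. First, the results would not apply to women with GSM and sexual dysfunction, and no later analysis could recover that population. Second, every participant would start the FSFI above the dysfunction cut-off, so a move out of dysfunction, as the protocol defines it, could not be observed in anyone.

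**Working it through.** **Inputs**

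- Entry rule: FSFI > 26.55 (Eligibility criteria, item 5).
- Definition of sexual dysfunction: FSFI < 26.55 (Outcomes, FSFI description).
- Planned total: 42 (Sample size).

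**The two rules side by side**

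| FSFI total | Dysfunction under Outcomes? | Admitted by the number in item 5? | Admitted if dysfunction (as Outcomes defines it) and the number are both required? |
|---|---|---|---|
| Below 26.55 | Yes | No | No |
| Exactly 26.55 | No (not below) | No (not above) | No |
| Above 26.55 | No | Yes | No |

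The set of scores that are both above and below 26.55 is empty. Three readings of item 5 are therefore possible:

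1. By its number: everyone admitted is outside the definition. With the planned total filled, that is 42/42 = 100% without dysfunction, and 0% of women with dysfunction are eligible.
2. By its number and its words together, using the Outcomes definition: nobody is eligible.
3. By its words alone, ignoring the number: the intended women are eligible, but then the printed threshold is not being used.

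**Which direction fits the rest of the document.** The aim, the Conclusion, the FSFI description and the words of item 5 all point to women with dysfunction. Only the phrase giving the inequality points the other way. Nothing in the article reverses the scale or explains that phrase.

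**Does the sample size depend on this?** The plan states "we will consider a power of 80%, an alfa error of 5%, and an effect size of 0.23", and from this that "a total of forty-two individuals will participate in the study". The calculation is for a repeated-measures ANOVA, within-between interaction, with k = 3 groups. The number of measurements m, the correlation ρ and the sphericity correction ε are not stated, so I assumed m = 3, ρ = 0.5 and ε = 1:

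- Noncentrality: λ = f² × N × m / (1 − ρ) = 0.23² × 42 × 3 / 0.5 = 13.33
- Numerator df = (k − 1)(m − 1) = 2 × 2 = 4
- Denominator df = (N − k)(m − 1) = 39 × 2 = 78
- Power at N = 42: 0.822. The smallest N reaching 80% is 41, which becomes 42 in three equal groups.

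This reproduces the stated 42 under those assumptions. Other values give other totals in three equal groups: with ρ = 0.5, m = 2 gives 51 and m = 4 gives 36; with m = 3, ρ = 0.3 gives 57 and ρ = 0.7 gives 27. The FSFI cut-off does not enter the formula, so correcting its direction leaves the total unchanged.

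**The case against.** The strongest reply is that this is an obvious one-word slip. Item 5 itself says the woman must have sexual dysfunction, and the rest of the article agrees, so staff may well screen correctly. The article also condenses a fuller protocol that is not shown and may have the right direction. On this view, 42 of 42 is the result of one reading and not an established fact.

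That is fair as far as it goes. The figure is conditional on the printed number being applied, and the document does not show that anyone was screened that way. But the article does not leave the criterion to another document: it states it, and states it wrongly. A reader cannot tell which direction was used.

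Two narrower objections also stand. The primary outcome is vaginal manometry, urinary incontinence has its own entry criterion, and the groups are randomised, so the between-group comparison on manometry stays internally valid whoever is enrolled. And the article does not give the FSFI maximum, so the room left for improvement above 26.55 cannot be quantified from it. What is certain is only that all baseline scores would lie above the cut-off. These points limit how far the damage reaches; they do not remove the contradiction.

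**Conclusion.** The concern holds. The entry criterion and the outcome definition contradict each other on the direction of the FSFI cut-off, and the entry criterion is the one at odds with the trial's stated aim. If the number is applied as printed, 100% of participants (42 of 42) fall outside the protocol's definition of sexual dysfunction and 0% of women within it are eligible. That result follows by logic from the two statements and needs no outside knowledge of FSFI scoring. It rests on one assumption: that screening follows the printed threshold.

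The damage falls on the population the results apply to and on the interpretation of the FSFI outcome. It does not fall on the sample size or on the internal validity of the manometry comparison. It must be corrected because a wrongly enrolled population cannot be repaired in the analysis.

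**What to change.** - Change item 5 to require an FSFI total below 26.55, so that it matches the definition in the Outcomes section.
- State how a score of exactly 26.55 is handled, and use the same rule for entry and for the outcome classification.
- Check the full protocol, the registry entry and any screening form for the same wording, and correct them where it appears.
- Check every woman already screened against the corrected rule before randomising more, and report which direction was in fact applied.

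The cost is one word in the criterion, a sentence on the boundary score, an ethics and registry amendment, and a review of screening records. No extra participants, visits or procedures are needed, and the planned total of 42 is not altered by this change.

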**Figure 2 fig-2:**
[figure not shown]
Protocol description illustration. Created in Canva.

The PFMT group associated with photobiomodulation will perform the physical exercise, and right after exercising, the women will use the photobiomodulation device (Fluence Maxx-HTM®, Alpharetta, GA, USA) (Fig. 3). Table 1 demonstrates the LED equipment characteristics and irradiation parameters. The vaginal atrophy protocol will start with 25 J/cm^2^, continuous emission mode, during 450 s. A red, low-intensity light with a wavelength of 660 nm depicts the emission. The protocol is in accordance with previous studies (Lanzafame, de la Torre & Leibaschoff, 2019). The women will be in a lithotomy position during the photobiomodulation intervention. So, a probe covered by a nonlubricated condom but with a lubricant gel, will be inserted in the vaginal canal. Before starting the photobiomodulation intervention, the researcher will wear glasses and request the women to wear them.

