The VHI scale evaluates vaginal atrophy by assessing the vaginal humidity, vaginal liquid volume, vaginal elasticity, pH, and vaginal epithelium integrity. Values below 15 indicates that vaginal mucosa is atrophic. To evaluate the pH, we will position a universal pH tape (MERCK**®** (MColorpHastTM, Merck, Rahway, NJ, USA) in the right vaginal wall during 1 min without contact with the cervix or cervical mucus. A pH below and above five indicates normal and atrophy vaginal trophism, respectively (Bachmann & Nevadunsky, 2000). All the instruments that will measure the outcomes of the study are in accordance with the published license. Figure 4 illustrates the evaluation process.

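### The entry criteria do not establish the genitourinary syndrome of menopause (GSM), so the women enrolled may not match the population named in the aim and conclusion

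*Protocol article*

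**What the plan says.** The Introduction defines GSM as "characterized by the presence of signs and symptoms generated from estrogen deficiency in the female genitourinary tract" and adds: "The main signs and symptoms include vaginal atrophy and dryness, vulvovaginal discomfort, and sexual difficulties, such as lack of lubrication and dyspareunia". It also associates GSM with urinary dysfunction. The aim is to study "PFMT isolated and associated with photobiomodulation in women affected by GSM who present urinary and sexual dysfunctions", and the Conclusion projects its result onto women with GSM who have both kinds of dysfunction.

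The Eligibility criteria section is a numbered list of nine items:

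- age 45 to 65;
- natural menopause at least a year ago;
- no hormone therapy for at least 3 months;
- sexually active;
- sexual dysfunction by the female sexual function index (FSFI);
- "present urinary incontinence (UI) identified by the international consultation on incontinence questionnaire (short form) with a score higher than 1 point";
- no earlier pelvic floor exercise;
- no earlier photobiomodulation;
- a negative Pap smear.

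The Exclusion criteria remove women who cannot follow instructions, those with infectious or degenerative disease, and those with grade III or IV prolapse.

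Under Interventions, the light treatment is introduced with "The vaginal atrophy protocol will start with". Under Outcomes, the VHI has a stated threshold, "Values below 15 indicates that vaginal mucosa is atrophic", and a pH above five is read as atrophy. The Participants timeline section places both measures in the first evaluation of women who have already been included.

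**The concern.** The aim has two parts: the woman has GSM, and she has urinary and sexual dysfunction. The list puts only the second part into effect, together with menopausal and hormone status. No item asks for a GSM diagnosis, atrophy, dryness, vulvovaginal discomfort, a low VHI or a raised pH, and none restricts the cause of the incontinence. Recruitment is at a urogynecology clinic, where incontinence of other origin can be expected.

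Two things are at stake. First, a conclusion worded for women with GSM would rest on a mixture whose make-up the criteria do not fix. Second, the VHI is a secondary outcome, and women with little or no atrophy at baseline may have less room to improve on it, which would pull the average difference between active and sham towards zero.

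**Working it through.** **1. Definition against criteria.**

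| Element of GSM in the Introduction | Entry criterion that tests it |
|---|---|
| Estrogen deficiency | Indirectly: natural menopause for at least 1 year, no hormone therapy for at least 3 months |
| Vaginal atrophy, dryness | None; VHI and pH serve only as outcomes |
| Vulvovaginal discomfort | None |
| Sexual difficulties (lubrication, dyspareunia) | FSFI total, which sums six domains including desire and satisfaction |
| Urinary dysfunction | Incontinence score above 1 on a 0 to 21 scale, any type or cause |
| Symptoms generated by the deficiency | None |

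A postmenopausal woman with a normal VHI, a normal pH, incontinence of another origin and a low desire score could meet every item. The FSFI item also needs attention: the Eligibility criteria ask for a score above 26.55, while the Outcomes section classes scores below 26.55 as dysfunction. Those two statements must be reconciled. Read literally, the list loses even its sexual-symptom link to GSM.

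**2. The planned sample size.** Inputs from Sample size, Randomization and Statistical analysis: effect size f = 0.23, alpha 5%, power 80%, k = 3 groups, m = 3 analysed time points. Assumed because not stated: correlation rho = 0.5 and sphericity. For the within-between interaction:

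- lambda = f² × N × m / (1 − rho) = 0.0529 × 42 × 3 / 0.5 = 13.33
- df1 = (3 − 1)(3 − 1) = 4; df2 = (42 − 3)(3 − 1) = 78

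Power at N = 42 is 82.2%, and 42 is the smallest multiple of three that reaches 80%. The stated total reproduces. Relabelling the population does not change it.

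**3. Possible dilution of a VHI effect.** Let p be the share of enrolled women without atrophy, and g the fraction of the full VHI benefit that they can still obtain. The article gives neither. Then

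mean effect / effect in atrophic women = 1 − p(1 − g),

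and, for an unchanged standard deviation, the sample size needed scales as 1 / [1 − p(1 − g)]².

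| p (assumed) | Women of 42 | g (assumed) | Relative effect | Sample size multiplier |
|---|---|---|---|---|
| 0.2 | 8.4 | 0 | 0.80 | 1/0.64 = 1.56 |
| 0.5 | 21 | 0 | 0.50 | 1/0.25 = 4.00 |
| 0.2 | 8.4 | 0.5 | 0.90 | 1/0.81 = 1.23 |
| 0.5 | 21 | 0.5 | 0.75 | 1/0.5625 = 1.78 |

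The Introduction's figure, "Approximately 40% to 50% of women in physiological menopause experience symptoms associated with the GSM", does not supply p. It refers to all women in natural menopause, not to those who also have incontinence and sexual dysfunction.

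**4. Size of a baseline VHI subgroup.** Under the same range of p, 21 to about 34 of the 42 women would have a VHI below 15, or about 7 to 11 per arm.

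**The case against.** The strongest reply is that the criteria do select on GSM features. The Introduction counts sexual difficulties among the main symptoms and links GSM to urinary dysfunction, and the list requires both in postmenopausal women off hormone therapy. The Abstract adds that the symptoms are to be related to menopause. This stands in part: the criteria enrich for GSM. But no item turns that relation into a test, and the list is presented as the criteria by which women will be recruited.

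A full protocol might describe clinical confirmation of GSM. That is possible, but the article gives VHI and pH with their cut-offs and assigns them to evaluation after inclusion.

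Three stronger readings are tempting, and the article supports none of them.

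- A reader might infer that the trial cannot answer its question. Randomisation protects the comparison whatever the case mix, the aim is exploratory, and baseline VHI and pH allow the mixture to be described.
- A reader might infer that the primary outcome loses power. Manometry measures muscle pressure, the rationale for photobiomodulation includes effects on muscle, and nothing shows that women without GSM would not respond.
- A reader might infer that women with a VHI of 15 or more cannot improve, or do not have GSM. The article uses 15 to classify mucosa as atrophic. It is not stated as a ceiling, and atrophy is only one of several GSM features. For the same reason, requiring a VHI below 15 would be a debatable narrowing rather than an obvious correction.

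**Conclusion.** The point holds as a mismatch between the stated and the selected population. Followed as written, the criteria yield postmenopausal women off hormone therapy with incontinence and, subject to the FSFI reconciliation, sexual dysfunction, an unknown share of whom have GSM. Internal validity and the manometry analysis are not affected. The harm lies in what the conclusions can be applied to, with possible dilution of the VHI effect. Across the assumed ranges (20% to 50% without atrophy, and none or half of the benefit available to them), the VHI effect would be 50% to 90% of its size in atrophic women. The true figure is unknown and could be smaller or nil. The matter is worth correcting because it changes what the trial can claim and costs little.

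**What to change.** Preferred: in the aim and conclusion, describe the population as postmenopausal women with urinary incontinence and sexual dysfunction. Report the share with a baseline VHI below 15 or a pH above 5. Pre-specify an exploratory analysis by baseline VHI (below 15 versus 15 or more), and let any statement about atrophy or GSM rest on it. The cost is narrower claims, some rewording and one added analysis. With 42 women that analysis has low power and can only be descriptive.

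Alternative: add a criterion saying how GSM is established before randomisation, using the protocol's own VHI or pH definitions. VHI and pH would then have to move to screening, recruitment would be slower, and women whose GSM is mainly urinary or sexual might be left out.

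Under either option, reconcile the direction of the FSFI cut-off between Eligibility criteria and Outcomes. The total of 42 does not change.
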